## Abstract

**Background:**

With the increase in the elderly population, a growing number of chronic degenerative diseases and a greater dependency on caregivers have been observed. Elderly persons in states of frailty remain more susceptible to significant health complications. There is evidence of an inverse relationship between plasma levels of inflammatory mediators and levels of functionality and muscle strength, suggesting that muscle-strengthening measures can aid in inflammatory conditions. The purpose of this study will be verified the effect of a muscle-strengthening program with load during a ten-week period in pre-frail elderly women with attention to the following outcomes: (1) plasma levels of interleukin-6 (IL-6) and tumor necrosis factor alpha (TNF-α), (2) functional capacity and (3) knee extensor muscle strength.

**Methods/Design:**

The study design is a randomized crossover clinical trial evaluating 26 elderly women (regardless of their race and/or social condition) who are community residents, older than 65, and classified as pre-frail according to the criteria previously described by Fried et al. (2004). All subjects will be assessed using the Timed up and go and 10-Meter Walk Test functional tests. The plasma levels of IL-6 and TNF-α will be assessed by ELISA (*enzyme-linked immunosorbent assay*) with high sensitivity kits (Quantikine^®^HS, R&D Systems Minneapolis, MN, U.S.). Knee extensor muscle strength will be assessed using the *Byodex System 3 Pro*^*® *^isokinetic dynamometer at angular speeds of 60 and 180°/s. The intervention will consist of strengthening exercises of the lower extremities at 50 to 70% of 1RM (maximal resistance) three times per week for ten weeks. The volunteers will be randomized into two groups: group E, the intervention group, and group C, the control group that did not initiate any new activities during the initial study period (ten weeks). After the initial period, group C will begin the intervention and group E will maintain everyday activities without exercising. At the end of the total study period, all volunteers will be reassessed.

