## Methods/Design

The general objective of the study will be verified the effect of a program of resistance exercises at 75% RM on the functional capacity, knee extensor muscle strength, and to measure the plasma levels of IL-6 and sTNFr in pre-frail elderly women.

Questions/Hypotheses

1. Among pre-frail elderly women, will changes occur in the plasma levels of the inflammatory mediators IL-6 and sTNFr, functional capacity and knee extensor muscle strength after completing a program of resistance exercises at 75% of 1RM, three times a week, for 10 weeks?

2. In a follow-up three months after finishing the training, will there be modifications in the functional capacity, knee extensor muscle strength and the plasma levels of IL-6 and sTNFr in pre-frail elderly women?

3. Is there a correlation between functional capacity, knee extensor muscle strength and plasma levels of IL-6 and sTNFr before and after a training program with load in pre-frail elderly women?

The study design is a blind randomized crossover clinical trial. Participants will be recruited from two universities. An initial assessment will be undertaken after recruitment and prior to randomization into either experimental or control group. Participants in the experimental group will receive an exercise program, three times a week, during ten weeks. Participants in the control group will receive no physiotherapy intervention. Outcomes will be measured again after ten weeks to reflect the immediate effect of the intervention. Then, the experimental group will receive no physiotherapy intervention and the control group will receive the same exercise program. Outcomes will be measured again to reflect longer-term outcomes from experimental group and the immediate effect of the intervention in the control group (Figure 1). This allows verification of the existence of a change and/or variable correlations specifically due to the intervention, and not due to the time factor and/or changes in the aging process. Furthermore, it allows verification of the existence of variable changes after finishing the training. Additionally, from an ethical point of view, it guarantees that the volunteers receive the same treatment. The outcome measures will be collected by a physiotherapist who was blind to group allocation. The responsible for the intervention will not know about the assessment. The study was approved by the ethical committee of the university and informed consent procedures were taken.

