### Sample

Twenty-six women, regardless of their race and/or social class, above the age of 65 who are community residents and classified as pre-frail according to the criteria established by Fried et al. (2001) will be selected for inclusion in the study. These volunteers will be randomly divided into two groups (control = C and experimental = E) of 13 volunteers each. This population was chosen based upon the assumption that pre-frail elderly people appear to respond better to interventions, resulting in a greater possibility of modifications that influence muscle response.^3 ^Demographic characteristics (age, race, school level, height, weight and body mass index) will be collected from all the participants.

Elderly women who meet one or more of the following criteria will be excluded from the study: previous lower extremities orthopedic surgery, a history of fractures within the past year, an inability to walk unaided, carriers of neurological diseases, diagnosed acute inflammatory disease that could interfere in the assessments and the program, tumor growth in the last five years, current use of immunomodulating medications and cognitive impairment based on the mini-mental state examination [31].

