After ten weeks, all the volunteers will be reevaluated with the same tests and parameters conducted in the first assessment. After this reevaluation, the groups will switch and those women who had completed the exercise program (experimental group) will now remain inactive. Those women who had previously been inactive (control group) will begin the same resistance program the experimental group had performed (Figure 1).

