### Sample size

The sample size was calculated after a previous pilot study with 12 participants, considering a confidence interval of 95%, a bilateral hypothesis test, a significance level of 0.05 (type I error), a power of 80% (type II error) and a crossover design for a statistical analysis of ANOVA. First, we calculated the size effect (f) for the partial ANOVA for the 12 participants, according to Portner & Watkins [39]. We use the functional performance (time in seconds of the TUG). We considered two freedom degrees and a power of 80%. It was determined that, considering a moderate effect size (0.5) for a minimum clinically significant difference, 13 volunteers will be needed in each group.

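### The trial is labelled and sized as a crossover, but group E's second period is post-training follow-up and no randomised between-group contrast is named for the training effect

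*Protocol article*

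**What the plan says.** All places are in the protocol article.

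- **Label.** The Abstract states: "The study design is a randomized crossover clinical trial evaluating 26 elderly women". The Methods/Design section repeats it: "The study design is a blind randomized crossover clinical trial". The last part of the Background uses the same term.
- **Allocation.** Under Sample: "These volunteers will be randomly divided into two groups (control = C and experimental = E) of 13 volunteers each".
- **Switch.** After the ten-week reassessment the groups change over. The Abstract says: "After the initial period, group C will begin the intervention and group E will maintain everyday activities without exercising". Under Intervention: "those women who had completed the exercise program (experimental group) will now remain inactive". No washout is stated.
- **Role of the second period.** Methods/Design says: "Outcomes will be measured again to reflect longer-term outcomes from experimental group and the immediate effect of the intervention in the control group". Study question 2 asks whether outcomes are modified three months after training ends.
- **Claim for the design.** The same section says the design lets change be attributed to the intervention rather than to time or ageing.
- **Sizing.** The Sample size section gives "a significance level of 0.05 (type I error), a power of 80% (type II error) and a crossover design for a statistical analysis of ANOVA", with an effect size of 0.5 on the Timed Up and Go, leading to 13 per group.
- **Analysis.** The Statistical analysis section plans an ANOVA over values before, after and three months after the intervention. It names no comparison of E with C and no period, sequence or carry-over term.

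**The concern.** In a crossover, each woman's second period supplies the condition she has not yet had. For group E that would be the untreated condition. Yet the protocol gives those weeks to a different purpose, namely what remains of the training effect. The same measurements can serve as untreated control only if nothing of the effect that bears on the estimate is left, and how much is left is itself one of the study questions.

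The attribution to the intervention rather than to time needs a contrast that supports it. A comparison of time points within women does not separate training from time. The crossover contrast does so only under an assumption about carry-over. The comparison of E with C at week 10 does so by randomisation alone, and the text does not name it as the main contrast. At stake are the size of the main effect estimate and the power claimed for it.

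**Working it through.** **1. The plan's own figure.** Inputs from the Sample size section: two-sided 0.05, power 80%, effect size 0.5 introduced as f, two degrees of freedom, 13 per group. The nearest match found is a one-way ANOVA with three independent groups (numerator df = 2, f = 0.5, noncentrality 0.25 × 3n). This gives 14 per group for 80.3% power and 76.9% at 13. It is close to 13 but is not a two-sequence crossover formula. Repeated measures at three times in one group need 15 women at correlation 0 and 9 at correlation 0.5. The text does not settle which formula was used.

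**2. What a crossover analysis would estimate.** Let θ be the true training effect, p a period effect, and L the fraction of θ still present in group E at the end of its second period. The protocol gives no L, so the range 0 to 1 is shown. Expected values at the end of each period, relative to baseline:

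| | Period 1 | Period 2 |
|---|---|---|
| Group E | θ | p + Lθ |
| Group C | 0 | p + θ |

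The standard estimator is half of [(E1 − E2) − (C1 − C2)].

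- *End-of-period values:* ½[(θ − p − Lθ) − (0 − p − θ)] = θ(1 − L/2).
- *Change from each period's own start:* group E changes by θ, then by p + Lθ − θ. Group C changes by 0, then by p + θ. So ½[(2θ − p − Lθ) − (−p − θ)] = θ(3 − L)/2.

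| L | End-of-period values | Change within period |
|---|---|---|
| 0 | 1.00 | 1.50 |
| 0.25 | 0.875 | 1.375 |
| 0.5 | 0.75 | 1.25 |
| 0.75 | 0.625 | 1.125 |
| 1 | 0.50 | 1.00 |

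Entries are multiples of θ. The period effect cancels in both. A simulation of 20,000 trials with 13 per group and a period effect gave 1.00, 0.75 and 0.50 (values) and 1.50, 1.25 and 1.00 (changes) at L = 0, 0.5 and 1. The second column overstates because group E's loss of its gain is counted as deterioration under control.

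As an illustration on end-of-period values, take 26 women, d = 0.5 and an assumed correlation of 0.7. Crossover power falls from 88.4% at L = 0 to 65.9% at L = 0.5 and 35.2% at L = 1.

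**3. The first-period contrast.** E − C at week 10 is θ − 0 = θ for any L. Power at 13 per group uses a two-sided t test with 24 df and noncentrality d√(13/2). Baseline adjustment at correlation ρ replaces d by d/√(1 − ρ²). For two equal groups f = 0.5 means d = 2f = 1.0. The correlations are assumptions.

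| Reading of 0.5 | Unadjusted | ρ = 0.5 | ρ = 0.7 | ρ = 0.8 |
|---|---|---|---|---|
| f (d = 1.0) | 68.7% | 80.6% | 92.8% | 98.3% |
| d | 23.2% | 29.3% | 40.3% | 53.2% |

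Taking off one more df for the covariate lowers each adjusted figure by less than 0.2 percentage points. The numbers per group needed for 80% are 17, 13, 10 and 7 (first row) and 64, 49, 34 and 24 (second row).

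**The case against.** The strongest reply is that the protocol never says group E's second period will be pooled as control. Methods/Design treats it as follow-up, and the Statistical analysis section lists it as a time point after training. The only hook for a crossover analysis is the label and the phrase "a crossover design for a statistical analysis of ANOVA". Model terms may properly sit in an analysis plan that is not shown. This stands: the bias is conditional, and a reader who infers that the plan commits to a biased estimate goes too far.

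Further inferences are tempting but not supported:

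- *The effect would be underestimated.* True only for end-of-period values. On within-period change the bias runs the other way unless the gain is fully kept.
- *The protocol expects the effect to persist.* Study question 2 asks neutrally whether outcomes are modified.
- *Carry-over is confounded with the period effect.* In the model above the difference in sequence totals, (E1 + E2) − (C1 + C2), is Lθ, and p cancels. Differential carry-over is aliased with the sequence effect and the treatment-by-period interaction.
- *The two groups get different off-training instructions.* The Intervention section calls both groups inactive when untrained, and the Abstract has group E keeping up everyday activities, much as the controls do.
- *The 13 per group relies on crossover efficiency.* The closest formula found has no within-woman gain.

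None of this removes the mismatch between the crossover label and sizing and the stated use of the second period. Nor does it supply a randomised contrast for the causal claim. Those are things the text states, not details left to a later document.

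**Conclusion.** The point holds in a limited form. The crossover label and sizing basis do not fit a design whose first sequence ends in post-training follow-up with no stated washout, and the planned ANOVA names no randomised comparison to support attribution to training rather than time.

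If a crossover analysis is used, the estimate lies between 0.50 and 1.00 of the true effect on end-of-period values, or between 1.00 and 1.50 on within-period change, as L runs over 0 to 1. It is unbiased only at L = 0 on the first scale and L = 1 on the second. That two ordinary analyses can err in opposite directions is a reason to fix the contrast in advance. The range rests on an assumed L and on a pooled analysis that the sizing section implies and the analysis section does not state. The week-10 comparison of E with C needs neither assumption.

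**What to change.** - Describe the trial as a randomised delayed-start (wait-list) trial in the Abstract, Background and Methods/Design.
- Name the week-10 comparison of E with C, adjusted for the baseline value already collected, as the main effect estimate.
- Report group E's second period as follow-up after training and group C's as an uncontrolled replication. Do not use group E's second period as a control.
- Reconcile Methods/Design, Sample size and Statistical analysis so that all three refer to this contrast.
- Replace the crossover sizing basis with the power of this contrast at 13 per group, say whether 0.5 is f or d, and give the assumed baseline correlation with its source.

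**Cost.** The schedule, the assessments and every woman's access to training are unchanged. The effect estimate uses one period instead of two, and the stated power may be less favourable. If 0.5 is f, 80% is reached at 13 per group only with baseline adjustment at a correlation of about 0.5 or more. If 0.5 is d, 13 per group falls well short at every correlation examined, and the text should say so.

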**Discussion:**

To demonstrate and discuss possible influences of load-bearing exercises on the modification of plasma levels of IL-6 and TNF-α and in the functional performance of pre-frail elderly women.

**Trial Registration:**

ISRCTN62824599

## Background

Changes in the world age pyramid are occurring rapidly, such that the elderly population is projected to grow by 550,000 per year and increase to one million per year by the year 2025 [1,2]. Aging is a multifaceted reality in which genetic, biological, social, cultural and psychological variables should be considered in the differing manifestations and outcomes [3]. Frailty is a syndrome of a multifactorial nature, characterized by a reduction in energy reserves and by a decreased resistance to stressors, resulting in a cumulative decline of the physiological systems, characterized by a trio of changes: sarcopenia, neuroendocrine deregulation and immune dysfunction [4]. Fried et al. (2001) proposed five criteria for the diagnosis of frailty in the elderly [5]. Early identification of the pre-frail elderly is important in order to institute therapeutic guidelines and interventions that can possibly prevent or minimize the conditions inherent to the state of pre-frailty, such as fluctuations in health and the risk of acute clinical complications [3-5].

Current studies demonstrate that the elevation in pro-inflammatory cytokines in the plasma of the elderly is associated with the development of the frailty syndrome, a reduction in mobility, and an inability to conduct the activities of daily life, a reduction in muscle strength and an increase in mortality [6-11].

Interleukin 6 (IL-6) is an expression in plasma increases during physiological aging, probably due to the reduction of sex hormones [3,12,13]. Tumor necrosis factor alpha (TNF-α) participates in the innate acute inflammatory response by inducing the secretion of chemokines, which stimulate a second wave of cytokines, including IL-6, IL-8 and C-reactive protein [14,15]. Greiwe et al. (2001) inferred that the systematic presence of TNF-α may contribute to the loss of muscle mass [16]. There is evidence that muscular modifications appear to be associated with high levels of pro-inflammatory cytokines, especially IL-6 and TNF-α [17,18].

Regular exercise has been indicated to promoting muscle strength and functionality in the elderly and helps reduce the levels of inflammatory mediators, with a reduction in the deleterious consequences of these cytokines on muscle loss [19-22]. However, the intensity, duration of exercise and the type of muscle contraction appear to be factors that influence this outcome, though the exact mechanism is still undetermined [19,23]. There are some evidences that IL-6 could be produced from muscle contractions and that its release was dependent on the intensity of the muscle activity and the number of muscle fibers involved in the contraction, specifically the concentric and the eccentric contraction [19]. In this case it could be called miokine. They inferred that IL-6 release probably occurred through a route independent of the release of TNF-α. This cascade would result in the inhibition of the deleterious muscular effects caused by the TNF-α released systematically during sub threshold chronic inflammation [19]. Febbraio et al. (2002) suggested that the release of IL-6 could be stimulated by calcium (Ca^2+^) as a means of maintaining metabolism in homeostasis, specially in eccentric and concentric contraction [23]. However, there is still no scientific evidence concerning which mode of muscle contraction--eccentric or concentric--is optimal in promoting modifications in the plasma levels of these cytokines [19,23]. For this reason, we would like to know what happens to the new exercise program with a concentric contraction.

Some exercise programs have been proposed with the intent of minimizing the loss of muscle strength in the elderly and its functional consequences [22,24-26]. In a randomized clinical trial, Kryger et al. (2007) demonstrated earlier gains in muscle strength in elderly persons after the execution of an exercise program and there was also an increase in the transverse section area and in the percentage of type II fibers, as analyzed by a muscular biopsy [27]. However, the release of inflammatory mediators after this exercises programs is already unclear. In relation to the inflammatory mediators, Plomgaard et al. (2005) reported that IL-6 could be produced from muscle contractions and that its release was dependent on the intensity of the muscle activity and the number of muscle fibers involved in the contraction [28]. They inferred that IL-6 release probably occurred through a route independent of the release of TNF-α, inducing anti-inflammatory activity by the release of IL-1ra and IL-10.

Given this information, it can be postulated that interventions that promote the strengthening of large muscle groups may modify the plasma levels of IL-6 and TNF-α, as well as improve the activity and functional performance of elderly persons [29,30]. These modifications would be of great benefit in the prevention and treatment of disease in the elderly, since many of their issues initially manifest as a reduction in functional activity and independence. However, the literature is unanimous in pointing out that new studies should be conducted to verify the type of muscle contraction and the ideal intensity and duration of an exercise program to increase muscle strength, and to investigate its impact on the plasma levels of IL-6 and TNF-α and functionality in the elderly. The rationale is to propose kinesiotherapeutic interventions that can promote the improvement of muscle strength while decreasing the release of inflammatory mediators, sarcopenia and functional disability. Intervening in this cycle will possibly contribute towards improved functional performance of daily activities, a reduced risk of falling, improvement in the quality of life and a reduced risk of the frailty syndrome.

Thus, this randomized crossover clinical trial was proposed with the objective of verifying the effect of a program of muscle strengthening with load during a ten week period in pre-frail elderly women with attention to the following outcomes: (1) functional ability, (2) knee extensor muscle strength and (3) plasma levels of IL-6 and TNF-α. The study hypothesis is grounded in the assumption that exercising with 75% of the maximum load at a frequency of three times per week for 10 weeks may be sufficient to provide strength gains, and consequently improve functional ability and reduce the plasma levels of IL-6 and TNF-α.

This project has financial support from the Conselho Nacional de Desenvolvimento Científico e Tecnológico - CNPq, Brasília, Brasil.

Clinical Trial Registration: ISRCTN62824599.

## Methods/Design

The general objective of the study will be verified the effect of a program of resistance exercises at 75% RM on the functional capacity, knee extensor muscle strength, and to measure the plasma levels of IL-6 and sTNFr in pre-frail elderly women.

Questions/Hypotheses

1. Among pre-frail elderly women, will changes occur in the plasma levels of the inflammatory mediators IL-6 and sTNFr, functional capacity and knee extensor muscle strength after completing a program of resistance exercises at 75% of 1RM, three times a week, for 10 weeks?

2. In a follow-up three months after finishing the training, will there be modifications in the functional capacity, knee extensor muscle strength and the plasma levels of IL-6 and sTNFr in pre-frail elderly women?

3. Is there a correlation between functional capacity, knee extensor muscle strength and plasma levels of IL-6 and sTNFr before and after a training program with load in pre-frail elderly women?

The study design is a blind randomized crossover clinical trial. Participants will be recruited from two universities. An initial assessment will be undertaken after recruitment and prior to randomization into either experimental or control group. Participants in the experimental group will receive an exercise program, three times a week, during ten weeks. Participants in the control group will receive no physiotherapy intervention. Outcomes will be measured again after ten weeks to reflect the immediate effect of the intervention. Then, the experimental group will receive no physiotherapy intervention and the control group will receive the same exercise program. Outcomes will be measured again to reflect longer-term outcomes from experimental group and the immediate effect of the intervention in the control group (Figure 1). This allows verification of the existence of a change and/or variable correlations specifically due to the intervention, and not due to the time factor and/or changes in the aging process. Furthermore, it allows verification of the existence of variable changes after finishing the training. Additionally, from an ethical point of view, it guarantees that the volunteers receive the same treatment. The outcome measures will be collected by a physiotherapist who was blind to group allocation. The responsible for the intervention will not know about the assessment. The study was approved by the ethical committee of the university and informed consent procedures were taken.

